## DESCRIPTION OF RESEARCH PROTOCOL (PARENT STUDY)

## 1. Study Design

We propose a prospective, randomized controlled trial assessing the efficacy of Tai Chi mind-body movement therapy as an adjunct to standard care in patients with chronic stable heart failure. We will compare a twelve-week Tai Chi program to an education attention control. This study will be named “NEXT-HEART Study”, which is short for **N**ew **Ex**ercise **T**ai Chi and **H**eart **E**ducation: **a R**andomized **T**rial. Measurements at baseline, 6 and 12 weeks will include quality-of-life and behavioral/psychosocial assessments, six-minute walk test, and neurohormone/cytokine blood tests. Metabolic bicycle stress test will be done at baseline and 12 weeks only. In addition, we will conduct a brief follow-up phone call at 6 months to assess current health status, quality of life using the Minnesota Living with Heart Failure Questionnaire, use of healthcare (numbers of hospitalizations and emergency department visits since the 12-week interview), and practice of Tai Chi and other exercise.

Figure 1: Study Flow Diagram

## Subject Selection

The sample will be identified from the ambulatory clinics at three main institutions: Beth Israel Deaconess Medical Center (BIDMC), Brigham and Women’s Hospital (BWH), and Massachusetts General Hospital (MGH). In addition to the two advanced HF specialty clinics (BIDMC and BWH) utilized in our pilot, we will also be recruiting from the primary care and cardiology clinics at each of the hospitals and affiliated community practices. The HF clinics combined see approximately 4000 patients per year. For our pilot study, we were able to enroll 30 patients over 1 year from two clinics with very minimal recruiting resources.

Hebrew Senior Life (HSL): We will also recruit eligible subjects from Hebrew Senior Life in Roslindale and two community housing facilities associated with HSL: Jack Satter House in Revere and the Simon Fireman Community in Randolph.

Most sites are concentrated in the same 3-block radius on the Harvard Longwood Medical Campus. The MGH is located approximately 3 miles from Longwood with a shuttle bus available between sites every 15 minutes. In addition, we will advertise the study via newspapers and flyers.

As HF is primarily a disease of the elderly, we expect to have mainly a population >60 years of age. We do not expect to have many patients below the age of 30, although this is theoretically possible with entities such as peripartum cardiomyopathy. Based upon our pilot data, we expect that more than 50% of patients will be ≥65 years of age, and over 80% will be ≥55. Patients will be excluded if they cannot safely complete the necessary testing measurements (such as exercise stress testing). We will recruit both men and women, as well as participants of all races and ethnicities.

**Subject Incentives**

Patients will be paid $200 for participating ($100 at 6 weeks and $100 at study end). The study may also facilitate transportation to and from study-related visits if logistical or financial constraints impair the patients’ ability to participate. Subjects recruited from Hebrew Senior Life Facilities will be paid $250 for their participation ($125 at 6 weeks and $125 at study end). Because classes will be held on site at Hebrew Senior Life (HSL) Facilities and we do not have to pay for parking, we are able to increase the incentives for subjects participating at these facilities.

At the end of the study, we will offer patients randomized to the education control group Tai Chi classes at no costs for 3 months as a courtesy. For the Tai Chi group, we will offer subjects the opportunity to continue taking Tai Chi. Tai Chi subjects may attend one additional 3-month Tai Chi program (free of charge) within 6 months of completing intervention class, but will be required to pay their own parking expenses.

### Eligibility Criteria

We will recruit patients using the following inclusion and exclusion criteria.

**Inclusion Criteria:**

- Adult patients with chronic HF
- Left ventricular ejection fraction ≤40%, by echocardiogram or by left ventriculogram in the past 2 years*
- Stable medical regimen, defined as no major changes in medication in the past 3 months
- New York Heart Association Class I, II, or III

**Exclusion Criteria:**

- Unstable angina or myocardial infarction in the past 3 months
- Major cardiac surgery within the past 3 months
- History of cardiac arrest in the past 6 months
- History of cardiac resynchronization therapy (CRT) in the past 3 months
- Unstable serious ventricular arrhythmias
- Unstable structural valvular disease
- Current participation in a conventional cardiac rehabilitation program
- Diagnosis of peripartum cardiomyopathy within prior 6 months
- Inability to perform a bicycle stress test
- Lower extremity amputation, or other inability to ambulate due to conditions other than HF
- Severe cognitive dysfunction precluding informed consent and understanding of Tai Chi concept (MMSE ≤ 24)
- Inability to speak English
- Current regular practice of Tai Chi
- Participant randomized to Tai Chi in Tai Chi Pilot Study or current participant in other trial

*For patients who appear otherwise eligible for the study, but who have not had their ejection fraction (EF) measured in the past 2 years will be asked to undergo a limited echocardiogram at MGH to measure their current EF and confirm study eligibility. This will include patients such as those with a chronic stable low EF whose medical providers believe that the patient’s EF or condition has not changed enough to warrant an echocardiogram for clinical purposes. For such patients, informed consent will take place either prior to or during their echocardiography visit following the study procedures outlined in Procedures for Informed Consent.

*We will not exclude patients on the basis of their religious preferences or practices.*

Taking into account the general demographics of the 3 study institutions, we anticipate the following profile of patients with respect to women and minorities.

| **GENDER** | **MINORITIES** |
| --- | --- |
| White Women 53 | Whites 105 |
| African American Women 15 | African American 30 |
| All Women 75 | All minorities 45 |
| Percent female 50% | Percent minority 30% |

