### Statistical Analysis and Power

Prior to analyzing the outcomes, we will compare the randomized groups with respect to baseline demographic, functional, and clinical variables as well as known prognostic factors (such as baseline NYHA class and baseline peak VO2) using chi-square and Fisher’s exact tests. Although we do not expect any differences with proper randomization, any significant imbalances (p<.05) will be adjusted for in the statistical analyses. All analyses will be performed on an intention-to-treat basis.

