### Analysis Plan for Primary Specific Aims

To assess the adequacy of randomization, we will use Fisher’s Exact tests (categorical variables, e.g., sex, NYHA Class) and Wilcoxon rank-sum tests (continuous variables, e.g., age) to detect any differences in baseline characteristics between treatment groups.

Our three primary endpoints are change in exercise capacity and quality of life from baseline to 12 weeks using the six-minute walk, peak VO2 and MLHF score. Because we will recruit patients from 3 institutions, we will formally examine whether there is a site effect by performing Kruskall-Wallis tests to assess whether changes from baseline to 12 weeks differ by site for each outcome. In the event that we observe a site effect, we will proceed stratifying our analyses by site using van Elteren’s test. A priori, however, we do not expect to observe a site effect for a number of reasons, including the 3 institutions are academic tertiary care centers located in the same catchment area, they have similar patient profiles, and they apply the same standard of cardiac care by following ACC/AHA guideline. If no site effect is observed, we will proceed with our analyses by performing two-sample non-parametric Wilcoxon rank-sum tests to compare the distribution of change from baseline to 12 weeks between treatment and control groups for each outcome measure.

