### Additional Analyses

Other descriptive analyses: Clinical data obtained through patient interview (as well as medical record/automated utilization data used to track medical resource use for the cost analysis) will be analyzed using descriptive statistics. Particularly, we are interested in medication changes such as diuretic or beta-blocker dosage, unforeseen cardiac procedures such as pacemaker placement, cardiac hospitalization and ER visits that may be informative if there are clinically significant differences between the groups. In addition, patient report of physical activity outside of study sessions (as measured by the CHAMPS instrument) will be analyzed and presented descriptively.

Qualitative exit interview: Qualitative patient exit interviews will be professionally transcribed from audiotapes and coded using an inductive approach informed by grounded theory methods. We will identify passages in the transcripts that represent common themes or content categories relating to positive, negative, and neutral aspects of patients’ experiences with both Tai Chi intervention and education-attention control. Data will be analyzed and presented descriptively according to content categories.

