## RECRUITMENT AND CONSENT PROCEDURES

## Procedures for Patient Identification and Enrollment

To identify potential patients for enrollment, we will use on-site screening of patients at clinic visits; regular screening of potential patients using the electronic medical records; referral from physicians and other providers; newspaper advertisements; and flyers. All recruitment procedures will follow HIPAA guidelines.

Patients will be recruited from the primary care, heart failure and general cardiology clinics at the three participating institutions: Beth Israel Deaconess Medical Center, Brigham and Women’s Hospital, Massachusetts General Hospital, and affiliated community practices. At these institutions, we will solicit referrals from providers (physicians and nurse practitioners) practicing in these clinics and leave informational brochures and flyers in patient areas. The research nurse coordinator and research assistants will maintain constant contact with providers through email communication, monthly staff meetings, and regular site visits. We will pre-screen the electronic medical record to identify potential patients with an ejection fraction of ≤40%. With the provider’s permission, we will pre-screen patients with appointments from clinic appointment logs for study eligibility. We will also obtain from each provider whether they would like to us to ascertain approval to approach each eligible subject individually. For these providers, we will notify them of each eligible patient and request their permission to approach the patient to invite participation. We will also ask whether another physician is involved in the patient’s care who should be contacted for permission. However, some providers request that we only contact them once an eligible patient has expressed strong interest in study enrollment. For these providers, we will notify them of each eligible patient who expresses interest in study enrollment and ask whether there is another provider involved in the patient’s care who should be contacted for permission. At this juncture, providers have the opportunity to decline study participation for any reason.

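### The exclusions for cardiac rehabilitation, CRT and major cardiac surgery do not cover events already scheduled within the 12 weeks, which admits avoidable noise and possible contamination of the primary change scores

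*Protocol*

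**What the plan says.** Three items in the protocol's Exclusion Criteria concern treatments that could change exercise capacity or quality of life: "Current participation in a conventional cardiac rehabilitation program", "History of cardiac resynchronization therapy (CRT) in the past 3 months" and "Major cardiac surgery within the past 3 months". The first looks at the present and the other two look back. The one stability requirement, in the Inclusion Criteria, also looks back and covers drugs only: "Stable medical regimen, defined as no major changes in medication in the past 3 months".

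The outcome window lies after these screening windows. The Analysis Plan for Primary Specific Aims states: "Our three primary endpoints are change in exercise capacity and quality of life from baseline to 12 weeks". Under Statistical Analysis and Power, "All analyses will be performed on an intention-to-treat basis".

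Additional Analyses lists "unforeseen cardiac procedures such as pacemaker placement, cardiac hospitalization and ER visits" among events to be described. Under Procedures for Patient Identification and Enrollment, "providers have the opportunity to decline study participation for any reason".

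**The concern.** An event shortly before baseline can disturb the change score only through what is left of the recovery. An event shortly after baseline puts its whole effect by week 12 into the change score. As written, CRT two months before baseline excludes a patient, while CRT booked for two weeks after baseline does not. A patient referred to conventional rehabilitation and due to start the week after enrolment is likewise eligible.

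Two things are at stake. The first is precision: affected patients add variation unrelated to the study treatment, and a procedure may also cost the 12-week walk or bicycle test. The second is the contrast itself. The comparator is an education and social group. For a control patient who takes up conventional rehabilitation, the comparison moves towards Tai Chi against conventional exercise. If controls did this more often than Tai Chi patients, the difference on six-minute walk and peak VO2 would shrink.

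**Working it through.** **Text check.** Each inclusion and exclusion criterion was read for a planned, scheduled or anticipated event. None has one. Three other provisions might act as filters:

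- Unstable angina in the past 3 months and unstable valvular disease are excluded. This may remove some candidates for surgery, but not those booked for elective CRT or rehabilitation.
- Providers may decline for any reason. This is discretionary and does not mention planned procedures.
- Randomization is stratified by NYHA class only, so a booked event is balanced in expectation but not by design.

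The wording gap is therefore real. It rests on no stated figure.

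**Illustration of size, peak VO2.** Inputs from Sample Size Justification: difference 1.5 ml/kg/min, SD of change 2.1, 50 per arm, 20% dropout, 10% efficiency loss, Bonferroni over three endpoints.

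- Effective n per arm = 50 × 0.8 × 0.9 = 36.
- Alpha = 0.05/3 = 0.0167, taken as two-sided.
- Test: two-sample t, 70 degrees of freedom, noncentrality = difference / (SD × √(2/36)).

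*The plan's own figure.* It states 80% power. With dropout alone (40 per arm) the t calculation gives 0.771 and the normal approximation 0.788. With both losses (36 per arm) they give 0.717 and 0.738. The gap from 80% is a separate matter; 0.717 is used here only as the starting point.

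*Assumptions, not in the documents.* A share p of patients has the event, with p = 5%, 10% or 20%, and each affected patient gains 1.5 ml/kg/min, added to any effect of assignment.

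*Balanced uptake.* The difference stays 1.5 and the variance becomes 2.1² + p(1−p) × 1.5².

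| p | Added variance | SD | Power |
|---|---|---|---|
| 0 | 0 | 2.100 | 0.717 |
| 5% | 0.107 | 2.125 | 0.705 |
| 10% | 0.203 | 2.148 | 0.694 |
| 20% | 0.360 | 2.184 | 0.677 |

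At 1% and 2% power is 0.715 and 0.712.

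*Worst case: only controls take it up.* The difference becomes 1.5 − 1.5p, with the SD held at 2.1.

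| p in controls | Difference | Power |
|---|---|---|
| 5% | 1.425 | 0.665 |
| 10% | 1.350 | 0.609 |
| 20% | 1.200 | 0.492 |

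If half of this dilution arises, so that the difference is 1.5 − 0.75p, power is 0.691, 0.665 and 0.609.

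These figures use a gain in peak VO2 and fit rehabilitation best. Nothing comparable has been quantified for CRT or surgery, and the loss from missing 12-week tests is not included.

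**The case against.** The strongest reply is that nothing here is stated wrongly. The protocol gives no rationale for these windows. They sit beside myocardial infarction, cardiac arrest and unstable arrhythmia, so they can be read as safety or stability criteria, for which looking back is normal. This stands as a reason to call the point a refinement rather than an error. It does not remove the effect on the change score, which follows from the endpoint window whatever the criteria were for.

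The second reply is that a booking made before enrolment is a baseline attribute. Assignment comes after baseline testing, from sealed opaque envelopes in permuted blocks, so such bookings are balanced in expectation. This stands, and it is the main limit on the point. A reader might infer that the gap biases the trial towards no effect. The documents do not support that. Bias needs uptake that differs by arm. Patients know their assignment, and those given Tai Chi already have an exercise class, so a difference is plausible, but nothing in the protocol shows one. Tai Chi is also tested as an adjunct to standard care, so some care during follow-up belongs to the comparison.

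A reader might also see a contradiction between the word unforeseen in Additional Analyses and eligibility that admits foreseen procedures. There is none. That passage gives examples of events to describe and does not claim that every procedure is unforeseen. The section on medical utilization collects cardiac procedures without that qualifier.

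Finally, a stable drug regimen, the provider's right to decline and twice-weekly classes in both arms make high frequencies harder to credit, and the CHAMPS questionnaire would show outside activity. These are fair reasons for a modest estimate. They do not close the gap in wording.

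**Conclusion.** The point holds in a limited form. As written, the three exclusions admit a patient already scheduled for conventional rehabilitation, CRT or major cardiac surgery during the 12 weeks, and the effect of that event enters the primary change scores. The expected consequence is some extra variance and some missing 12-week tests.

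Under balanced uptake the illustrated loss of power for peak VO2 is about 1 to 4 percentage points at frequencies of 5% to 20% (0.717 to 0.705–0.677), and under 1 point at 1% to 2%. The fall to 0.492 needs two assumptions together: 20% of controls affected, and no Tai Chi patient taking up the same treatment. It should be read as an outer bound of this illustration, not as the likely size. All of these figures also assume a gain of 1.5 ml/kg/min per affected patient, although rehabilitation would start partway through the window.

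An analysis plan not shown here could define how such events are handled, but it would not change who is eligible. Minor priority: a cheap improvement, not a threat to the trial's validity.

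**What to change.** In the Exclusion Criteria, extend the three items to cover conventional cardiac rehabilitation, CRT or major cardiac surgery already scheduled within the 12-week study period. Add one question on this at screening, and allow such patients to be re-screened later under the existing criteria. This changes trial eligibility only; it does not withhold, delay or recommend any procedure or rehabilitation.

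The cost is one amended line per criterion, one screening question, and a few candidates deferred or lost from the recruitment pool.

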### Intervention

We will utilize the same Tai Chi protocol that we developed, refined, and successfully employed in our pilot study.This intervention, broadly based on a Tai Chi program developed by Wolf and colleagues for use in trials with elderly patients17 emphasizes essential Tai Chi movements that are both easily comprehensible and can be done repetitively in a flowing manner. The five chosen Tai Chi movements––*‘raising the power’*, *‘withdraw and push’*, *'grasp the sparrow's tail'*, *‘brush knee twist step’*, and *‘wave hand like clouds’* –– are based on the traditional Cheng Man-Ch’ing’s Yang-style short form. In addition to these five formal movements, the intervention includes a complementary set of traditional Tai Chi warm-up exercises and a 2 minute cool-down period with breathing exercises. These focus on loosening up the physical body, incorporating mindfulness and imagery into movement, increasing awareness of breathing and promoting overall relaxation of body and mind. This intervention was developed by [name] who has more than 25 years of Tai Chi experience.

Two senior Tai Chi students and certified graduates of a 2.5 year instructor training program developed by [name] will administer the Tai Chi intervention under [name] direction. Some instructors taught classes for the pilot study and have already gained experience working with a frail cardiac population and appreciate the unique set of challenges this population may bring. Prior to the start of the trial, [name] will conduct a series of trainings to review the protocol. Video analysis of mock group sessions will be used to ensure consistent application of the protocol.

Tai Chi classes will be conducted twice weekly for one hour each for 3 months (identical to the intervention used in our pilot study). Many prior Tai Chi trials have demonstrated clinical changes using a similar-length intervention.

Classes will be held at BIDMC, MGH Revere Community Health Associates, and other community-based facilities. These facilities are located in outpatient clinical space and thus, are fully equipped with medical emergency equipment and have immediate access to medical personnel. A nurse or study staff member certified in basic life support will be present at all classes. Chairs will be provided for seated warm-up exercises and resting, as well as for stability as needed when performing standing exercises. Throughout the 12-week program, the nurse or BLS-certified study staff member will maintain a log to document class attendance, and who completed the class with or without sitting down.

Hebrew Senior Life: Classes will be held in fitness centers located at Hebrew Senior Life Roslindale Campus, Jack Satter House, and Simon Fireman Community.

To facilitate logistical and transportation issues, we will offer classes at a variety of times, including weekday, weekend, and evening sessions. Of note, HF educational materials provided to the education control group (described below) will also be given to patients in the intervention group. Materials will be handed out weekly and briefly presented (3-5 minutes) by the study nurse or BLS-certified study staff member prior to the start of Tai Chi class.

| Table 1. Details of Proposed Tai Chi Intervention | | |
| --- | --- | --- |
| Week | Activities | Approximate Duration (min) |
| 1 | Introductory Session: Overview of Program  1. Description of class format  2. Demonstration of Tai Chi form  3. Expectations of participants  4. Tai Chi principles, philosophies   1. Participation in Warm-up Exercises 2. Cool-down (breathing) | 5  10  5  10  30  2 |
| 2-5 | Warm-up Exercises (Repeated during all sessions)   1. Standing:   a) “Drumming the body”  b) “Swinging to connect kidney and lungs”  c) “Washing the body with qi”  d) Standing meditation (w/ breathing)   1. Sitting:   a) Neck/Shoulder stretches  b) Arm/Leg stretches  c) Sitting meditation (w/ breathing)  Total Warm-up time  Tai Chi Movements   1. “Raising the Power” 2. “Withdraw and Push’   Cool-down (Breathing) | 6  3  3  3  6  3  6  30  5-10  5 per side  2 min |
| 6-9 | (Warm-up and Movements 1-2)  3. “Grasp Sparrows Tail”  4. “Brush Knee Twist Step”  Cool-down (Breathing) | 5 per side  5 per side  2 min |
| 10-12 | (Warm-up and Movements 1-4)  5. “Wave Hands Like Clouds”  Cool-down (Breathing) | 5-10  2 min |

